### Statistical analysis

The distribution of continuous data is rated for normality using residual-plot or by the Shapiro-Wilk W test. Normality can be reached by simple transformation (log, logit). Statistical comparison of paired data is performed with parametric or non-parametric method or by analysis of variance (ANOVA). Depending on the distribution, testing is performed with Mann-Whitney or Wilcoxon tests, respectively. The risk for Type I errors is reduced by reducing the significance level to 0.05 (alpha). A general summation goal will be used to avoid mass-significance by repeated measurements. In statistical measurements where multiple comparisons cannot be avoided, Duncan’s corrections (i.e. secondary outcome parameters) are performed. For MRI data, correction for multiple comparisons is performed with Bonferroni’s correction or the false discovery rate (FDR). For statistical comparison between categorical variables (i.e. psychometric data) the *X*^2^ test with Yates’ correction is performed.

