**Methods:**

This is a randomised, participant- and assessor-blinded, cross-over clinical trial. Thirty healthy volunteers (male:female ratio 1:1) will be randomised to general anaesthesia by either sevoflurane or propofol. Multimodal magnetic resonance imaging (MRI) of the brain will be performed before and after general anaesthesia and repeated after 1 and 8 days. Each magnetic resonance imaging session will be accompanied by cognitive testing and questionnaires on fatigue and well-being. After a wash-out period of 4 weeks, the volunteers will receive the other type of anaesthetic (sevoflurane or propofol), followed by the same series of tests. Primary outcomes: changes in T1-weighted 3D anatomy and diffusion tensor imaging. Secondary outcomes: changes in resting-state functional magnetic resonance imaging, fatigue, well-being, cognitive function, correlations between magnetic resonance imaging findings and the clinical outcomes (questionnaires and cognitive function). Exploratory outcomes: changes in cerebral perfusion and oxygen metabolism, lactate, and response to visual stimuli.

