#### Intervention day (day 0): pre-intervention procedure

The volunteer will be re-screened according to all inclusion and exclusion criteria. It will be ensured that the volunteer is fasting according to the recommendations of The Danish Society for Anaesthesia and Intensive Care Medicine (DASAIM), which are aligned with the guidelines from the European Society of Anaesthesiologists [45]; thus, 2 h of fasting are required for clear liquids and 6 h for all other oral intake. After changing into hospital clothing, baseline MRI scans will be performed (MRI 1). Cognitive testing will be performed, and the questionnaires MFI-20 and QoR will be filled out by the volunteer.

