### Data processing – MRI

T1-weighted 3D anatomical images will be pre-processed using the FreeSurfer imaging analysis suite (http://surfer.nmr.mgh.harvard.edu/). Other software packages and approaches for data analysis may also be applied. Diffusion-weighted images will be pre-processed using the FSL software package (http://www.fmrib.ox.ac.uk and http://fsl.fmrib.ox.ac.uk/fsl/fsl4.0/tbss/index). This includes inspection of image quality. The resulting data will then be processed via dtifit and tract-based spatial statistic. The re-aligned images will then be fed into bedpostx for local modelling of diffusion parameters. Using bedpostx in conjunction with track-based statistics (TBSS) allows us to model for crossing fibres. The re-aligned images will be fed into probtrackx2 for tractography between the anatomical areas mentioned above. Other software packages and approaches for data analysis may also be applied. Resting-state fMRI (rsfMRI) scans will be analysed using FSL MELODIC (http://fsl.fmrib.ox.ac.uk/fsl/fslwiki/MELODIC). Pre-processing steps will include spatial smoothing, motion correction, slice time correction, high-pass filtering and brain extraction. Individual component analysis (ICA) using data-defined and no less than 60 ICAs will be applied. RsfMRI scans will be co-registered initially to the individual T1w3D anatomical scans (after neutral flipping and brain extraction) and subsequently to MNI 152 brain atlas. A full quality assurance (QA) will be performed consisting of inspection of head movement (< 3 mm and < 3°), acceptable co-registration and inspection of image quality. Resting-state networks (RSNs) will be identified using dual regression. Noise reduction will be performed manually. Randomise command will be performed with a design matrix consisting of the paired *t*-tests with and without co-variates, i.e. age and gender. Results will be displayed upon the MNI-152 normal brain atlas after dimension change as *p* < 0.05 after correction for multiple comparison. Activated areas will be identified semi-automatically. Additional software and methods for data analysis may be applied. In addition, age, gender, physiological variables, blood tests and cognitive test scores, etc. may be used as co-variates in the analysis.

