### Sample size

We base our sample size estimations on the following primary end points: (1) changes in grey-matter volume, and (2) DTI changes. The volunteers will serve as their own controls.
(i)*Sample size estimation based on changes in grey-matter volume*: we base our sample size estimation for grey-matter volume changes on data extrapolated from the hippocampus. The mean volume of the hippocampus is approximately 2.50 mL (± 0.15 standard deviation (SD)) in the healthy population [54]. The pre-operative hippocampal volume has been found to be 6% smaller in patients suffering from POCD compared to patients not suffering from POCD [55]. We assume that GA will affect the grey-matter volume to a larger extent compared to e.g. vulnerability towards POCD. Thus, 25 subjects will be necessary to detect a difference of 8% in the hippocampal volume between groups, applying a two-tailed alpha value of 0.05, SD ± 10% and a desired power of 0.80(ii)*Sample size estimation based on DTI changes*: our sample size estimation for detection of DTI changes is also based on data extrapolated from the hippocampus. We assume a 10% change in mean diffusivity, since we expect GA to induce larger changes than, e.g. a learning task by video gaming [56]. With a significance level of 0.05, a power of 80%, a SD of ± 10%, this indicated a required sample size of 16 volunteers

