### Detection of differences between general anaesthesia methods

For detection of differences between GA methods, we estimate a 10% difference between the two GA methods with regard to both grey-matter changes and changes in DTI. With a significance level of 0.025 (Bonferroni corrected), SD ± 10% and a power of 80%, the sample size is 20. We therefore choose to include 30 volunteers to ensure sufficient power.

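### The sevoflurane–propofol contrast, framed as a difference in changes and tested by paired methods or ANOVA, would usually be more precise with the session baseline difference as a covariate

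*Protocol article*

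**What the plan says.** The abstract gives the endpoints as "Primary outcomes: changes in T1-weighted 3D anatomy and diffusion tensor imaging". The Sample size section bases its estimates on "1) changes in grey-matter volume, and (2) DTI changes". For the randomised comparison, the section on detecting differences between anaesthesia methods states "we estimate a 10% difference between the two GA methods with regard to both grey-matter changes and changes in DTI", and continues: "With a significance level of 0.025 (Bonferroni corrected), SD ± 10% and a power of 80%, the sample size is 20".

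The tests are in the Statistical analysis section: "Statistical comparison of paired data is performed with parametric or non-parametric method or by analysis of variance (ANOVA". Neither regression nor analysis of covariance is named there.

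Every volunteer has two baselines. On the intervention day "baseline MRI scans will be performed (MRI 1", with cognitive tests and questionnaires, and the Study session 2 section repeats session 1 apart from the agent.

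On covariates, the Data processing – MRI section names age and gender for the resting-state paired t-tests. It then adds that "age, gender, physiological variables, blood tests and cognitive test scores, etc. may be used as co-variates in the analysis". The list is open-ended. The baseline imaging value is not on it.

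**The concern.** If the endpoint is a change and the test is paired, the agent comparison becomes (post minus baseline under sevoflurane) minus (post minus baseline under propofol). This fixes the coefficient of the baseline difference at 1, whatever the data show, and brings the noise of two further scans into the contrast. Estimating the coefficient uses the same scans and usually leaves less residual variance.

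At stake is the precision of the second hypothesis, that sevoflurane produces the more pronounced changes. That is the question randomisation answers. The same holds for the between-agent contrasts of PASAT, TAP, CPT3, MFI-20 and QoR-15, which also have a baseline in each session.

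**Working it through.** **Inputs from the article.** Between-agent difference 10%, SD 10%, power 80%, alpha 0.025, 30 volunteers each receiving both agents. Two-sidedness is taken from the grey-matter calculation ("applying a two-tailed alpha value of 0.05, SD ± 10% and a desired power of 0.80"). The 8% grey-matter effect in the Sample size section serves as a sensitivity case.

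**Input not in the article.** r, the correlation across volunteers between the session difference (sevoflurane minus propofol) at baseline and the same difference after anaesthesia. It is varied from 0 to 0.99.

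**Step 1: reproduce the plan's figures.** The formula n = 2 × SD² × (z₁₋α/₂ + z₀.₈)² / δ² gives:
- 10%, alpha 0.025: 2 × (2.241 + 0.842)² = 19.01, so 20, as stated.
- 8%, alpha 0.025: 29.70, so 30, as stated.
- 8% and 10% at alpha 0.05: 24.53 and 15.70, so 25 and 16, as stated.

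This is the per-arm formula for two independent groups. Read as a paired calculation, it implies that the SD of the within-volunteer contrast is 10 × √2 = 14.14%. A paired formula with a contrast SD of 10% gives 10, 15, 13 and 8 in the same order and does not match.

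**Step 2: compare the variances.** Let V be the variance of a session difference, taken as equal at baseline and after anaesthesia.
- Difference of changes: V + V − 2rV = 2V(1 − r).
- Baseline difference as covariate: V(1 − r²), before the cost of estimating the slope.
- Ratio: (1 − r²) / [2(1 − r)] = (1 + r)/2.

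The saving is 50% at r = 0, 25% at 0.5, 15% at 0.7 and 5% at 0.9. Estimating the slope with 30 volunteers inflates the variance by about 1 + 1/27 and takes one degree of freedom.

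**Step 3: power at N = 30, two-sided alpha 0.025, noncentral t.** The change-score contrast has SD 14.14% and 29 degrees of freedom. The covariate version has SD 14.14 × √[(1 + r)/2] × √(28/27) and 28 degrees of freedom. No period term is included in either.

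| Analysis | r | 10% difference | 8% difference |
|---|---|---|---|
| Change scores | any | 92.8% | 76.5% |
| Covariate | 0 | 99.8% | 96.9% |
| Covariate | 0.5 | 97.4% | 86.7% |
| Covariate | 0.7 | 95.5% | 81.8% |
| Covariate | 0.8 | 94.3% | 79.4% |
| Covariate | 0.9 | 93.1% | 77.0% |
| Covariate | 0.95 | 92.4% | 75.8% |
| Covariate | 0.99 | 91.9% | 74.9% |

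Simulation with 20,000 runs per setting, at r = 0, 0.5, 0.8, 0.9 and 0.95, agrees to within 0.7 points. On variance alone the break-even is where (1 + r)/2 × 28/27 = 1, that is r of about 0.93.

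**Step 4: the other reading of the SD.** If 10% is already the SD of the paired contrast, change scores give 99.9% power at 10% and 97.4% at 8%, so there is little to gain.

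**The case against.** The strongest objection is that the article never says the baselines are subtracted. The quoted sentence offers a choice of methods for paired data. The word changes may name the effect of interest and not an estimator, and the Primary outcome section describes the measured volume, morphology and microstructure themselves. The covariate list is open-ended and further methods are allowed. All of this stands. A reader might infer that the plan commits to subtraction and rules out baseline adjustment; the text supports neither.

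It can also be said that this choice is normally left to an analysis plan, which is not shown. That would answer a complaint about missing detail. The point here is narrower. The article does state its endpoint form, its tests and its candidate covariates, and read together these lead to an analysis on which a specific improvement is available.

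Third, a difference of change scores is unbiased under randomisation, and about 93% power at the stated 10% exceeds the 80% target. This stands too. A reader might take the 76.5% at 8% as evidence of an underpowered comparison, but the article assigns 8% to grey-matter volume in its general sizing and 10% to the agent contrast.

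Fourth, the gain depends on an unknown r and is small or negative when r is high. That is correct, so the gain cannot be called free. However, r is not the test–retest correlation of the scans. Anatomy that is stable across all of a volunteer's scans cancels from both session differences, so highly repeatable MRI volumes do not by themselves imply a high r. Variation shared by scans within one session would raise it.

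**Conclusion.** The point holds as one of efficiency. It shows neither an error nor a power shortfall. On the natural reading of the article, the agent contrast is a difference of change scores, and adjusting for the baseline difference would generally be more precise. For the plan's 10% difference the gain is 7.0 points at r = 0, 4.6 at 0.5, 2.7 at 0.7 and 0.3 at 0.9. For the 8% sensitivity case it is 20.4, 10.2, 5.3 and 0.5 points. Near r = 0.95 there is a loss of under 1 point in both; at the extreme of r = 0.99 the loss is 0.9 points at 10% and 1.6 at 8%.

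These sizes rest on equal variances at baseline and after anaesthesia, on an r the documents do not give, and on a contrast SD of 14.1% that is inferred by matching the stated sample sizes.

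**What to change.** State how the two session baselines enter the between-agent comparison, before the blinded evaluation is opened. For each primary imaging measure and each post-anaesthesia scan, analyse the within-volunteer difference between agents in the post-anaesthesia value. Use the within-volunteer difference in the MRI 1 values as a covariate, with any period term that is planned. For voxelwise maps the baseline difference varies by voxel, so a voxelwise regressor is needed and not one fixed column. Apply the same model to the between-agent contrasts of PASAT, TAP, CPT3, MFI-20 and QoR-15. A Wilcoxon test takes no covariate, so say what happens to the adjustment if that route is chosen. Keep change from baseline for the within-agent hypotheses, which are themselves comparisons with baseline. It would also help to say whether the 10% SD refers to a single value, a change or a paired difference.

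The cost is analysis wording, one degree of freedom, and a small possible loss of power if r is very high (under 1 point near 0.95). No new measurements are needed, because both baselines are already in the schedule.

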## Methods

### Study design

This study is a participant- and assessor-blinded, randomised, cross-over clinical trial. The study population is healthy volunteers with a male:female ratio 1:1. Inclusion will continue until 30 volunteers have completed the study (See Table 1 for inclusion and exclusion criteria). The intervention is 2 h of GA. On each of two intervention days, the volunteer will be exposed to GA by either TIVA (propofol) or by a volatile agent (sevoflurane). Each volunteer will receive both types of GA during the study, the order being determined according to randomisation. Participants will be blinded to the type of GA. The assessment of outcome will be blinded during analysis.

**Table 1 Tab1:** Inclusion and exclusion criteria

**Inclusion criteria**	**Exclusion criteria**

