**Total score ≥ 4 predicts difficult intubation**			

### Outcomes

Outcome parameters will be measured before and after GA, and subsequently after 1 and 8 days. Possible differences can, thus, be assessed before and after GA, within each type of general anaesthesia, and between GA methods (sevoflurane vs. propofol).

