### Quality of Recovery-15 Questionnaire and Multidimensional Fatigue Inventory

The volunteers fill in the validated Quality of Recovery Questionnaire (QoR-15) [43] and the Multidimensional Fatigue Inventory (MFI-20) [42]. The QoR-15 questionnaire results in a score of 0–150. The MFI-20 covers aspects of general fatigue, physical fatigue, mental fatigue, motivation and activity in 20 statements with five-scale ratings of agreement.

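### The plan picks Mann-Whitney or Wilcoxon by distribution instead of by pairing, and assigns chi-square with Yates' correction to repeated psychometric scores; both rules need rewording

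*Protocol article*

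**What the plan says.** The design is paired throughout. Study design: "Each volunteer will receive both types of GA during the study, the order being determined according to randomisation". The Outcomes section plans comparisons before and after anaesthesia, within each agent and between agents, and Sample size adds: "The volunteers will serve as their own controls".

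The Statistical analysis section gives three relevant rules.

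- A general one: "Statistical comparison of paired data is performed with parametric or non-parametric method or by analysis of variance (ANOVA").
- Directly after it, the choice of rank test: "Depending on the distribution, testing is performed with Mann-Whitney or Wilcoxon tests, respectively".
- At its end, a rule for questionnaires and similar data: "For statistical comparison between categorical variables (i.e. psychometric data) the" chi-square test with Yates' correction is prescribed.

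On the scales, the questionnaire section says: "The QoR-15 questionnaire results in a score of 0–150". It describes MFI-20 as 20 statements, each rated on five levels. Both questionnaires and the cognitive tests are given before anaesthesia, after it, and 1 and 8 days later, in each of the two sessions.

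**The concern.** Two stated rules do not fit the data they govern.

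**Rank tests.** Mann-Whitney and Wilcoxon signed-rank are both used when normality is doubtful. What decides between them is whether the two sets of values come from different people or the same people. A rule that decides by distribution gives the analyst no valid criterion, and the closing word of the sentence refers back to nothing identifiable. An analyst could follow it and treat one volunteer's two values as two independent people.

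**Psychometric data.** The chi-square test compares counts between independent groups. Applying it to a 0–150 score means cutting the score into categories, which discards information, and then ignoring that the same volunteer sits in both columns. Yates' correction makes the test more conservative still. Even a truly binary repeated outcome would need a paired test such as McNemar's.

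The third hypothesis (lower well-being, more fatigue and poorer executive function, worse after sevoflurane) depends on these outcomes. This is the only test the section ties by name to psychometric data. If it is followed, a real difference could be reported as none.

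**Working it through.** **1. The plan's own figures.** With SD 10% and 80% power, the independent-means formula n = 2(z₁₋α/₂ + z₀.₈)² × SD²/δ² gives:

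- α 0.05, δ 8%: 2 × 2.8016² / 0.8² = 24.5, so 25
- α 0.05, δ 10%: 2 × 2.8016² / 1² = 15.7, so 16
- α 0.025, δ 8%: 2 × 3.083² / 0.8² = 29.7, so 30
- α 0.025, δ 10%: 2 × 3.083² / 1² = 19.0, so 20

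All four match the protocol. The formula equals a paired design with zero within-person correlation, so the sample size takes no credit for pairing. It also gives an anchor: the planned grey-matter effect is 8/10 = 0.8 SD.

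**2. Why ignoring pairing is conservative.** Let each measurement have SD 1, within-volunteer correlation ρ, and n = 30 pairs. The mean difference has standard error √(2(1 − ρ)/30). An unpaired test judges it against √(2/30) = 0.258, so it rejects only beyond about 1.96 × 0.258 = 0.506 SD, whatever ρ is. At ρ = 0.5 the true standard error is 0.183, and with no effect the unpaired test rejects with probability 2Φ(−0.506/0.183) ≈ 0.6%, not 5%. For a 0.5 SD shift the normal approximation gives:

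- paired: Φ(0.5/0.183 − 1.96) ≈ 78%
- unpaired: Φ((0.5 − 0.506)/0.183) ≈ 49%

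**3. Simulation of the named tests.** Inputs: 30 pairs (Study design: "Inclusion will continue until 30 volunteers have completed the study") and two-sided alpha 0.05. Assumed, because the protocol gives none of them: bivariate normal scores, ρ from 0 to 0.8, shifts of 0.3 to 0.8 SD, and a split at the pooled median to form the 2×2 table for chi-square. Power is shown as signed-rank / Mann-Whitney ignoring pairing / chi-square with Yates' correction:

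| Shift | ρ = 0 | ρ = 0.5 | ρ = 0.8 |
|---|---|---|---|
| 0.3 SD | 20 / 19 / 8% | 34 / 12 / 4% | 69 / 6 / 2% |
| 0.5 SD | 47 / 47 / 23% | 74 / 44 / 16% | 98 / 44 / 14% |
| 0.8 SD | 83 / 83 / 53% | 99 / 92 / 56% | 100 / 98 / 58% |

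With no effect, Mann-Whitney rejects in about 5% of trials at ρ = 0, under 1% at 0.5 and under 0.1% at 0.8. A separate run of 10,000 trials per scenario agrees with every cell of the table to within 3 percentage points.

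**4. The planned imaging effect at alpha 0.025.** For 0.8 SD, signed-rank against Mann-Whitney ignoring pairing gives 0.74 against 0.76 at ρ = 0, 0.96 against 0.83 at 0.5, and 1.00 against 0.91 at 0.8. The largest loss is about 0.14.

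**5. A valid use of Mann-Whitney.** Applied to within-volunteer period differences between the two sequence groups (15 each assumed, alpha 0.05, ρ = 0.8), Mann-Whitney has 66% power at 0.3 SD and 97% at 0.5 SD, against 69% and 98% for signed-rank in the same check. Its type I error is 4.6%.

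**The case against.** The best defence is that the section is compressed, not misconceived. The sentence just before the rank-test rule is about paired data, Wilcoxon and ANOVA are named, and the MRI data-processing section specifies paired t-tests for resting-state data. The rank-test sentence may simply list two tests. Mann-Whitney also has a legitimate place in a two-period cross-over, as step 5 shows, and a between-volunteer contrast can arise because the Missing data section keeps participants with only one session.

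This stands in part. It rules out four stronger readings:

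- **That the plan commits the trial to unpaired tests.** For the rank tests it only permits this.
- **That Mann-Whitney has no place here.** It is valid between sequence groups, although the section does not say that this use is meant.
- **That most of the power is lost.** For Mann-Whitney this holds only for small effects with high correlation. At 0.8 SD little is lost. The chi-square loss is heavier, but its size rests on a median split that the protocol does not specify.
- **That error rates are inflated.** With positive correlation the unpaired tests reject too rarely.

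The defence does not rescue the two rules themselves. Distribution remains the wrong criterion, and the psychometric sentence equates those data with categorical variables outright. These are statements in the text, not details left to a separate analysis plan.

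**Conclusion.** The point holds in this form. The rank-test rule uses the wrong criterion and so permits an independent-sample test on paired data. The psychometric rule prescribes an independent-sample test of counts for repeated numeric or ordinal scores.

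The chi-square rule is the more serious of the two. Under the assumptions above it has less than 60% power in every scenario, and it trails signed-rank even at zero correlation (0.5 SD: 23% against 47%). The Mann-Whitney loss runs from nil at zero correlation to severe at 0.3 SD with ρ = 0.8 (69% falls to 6%).

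The chi-square rule reaches secondary outcomes only. Whether the cognitive tests count as psychometric is not defined, but they are the natural candidates alongside the questionnaires. The rank-test rule is not limited to secondary outcomes by its wording, but at the planned imaging effect its cost is modest. This should be fixed; it does not undermine the trial.

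**What to change.** Reword the Statistical analysis section:

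- Within-volunteer contrasts use a paired t-test or, if the differences are clearly non-normal, Wilcoxon signed-rank on those differences. A mixed model with volunteer as random effect and agent, period and time as fixed effects is an acceptable alternative.
- Mann-Whitney is restricted to contrasts between the two sequence groups, including comparison of period differences.
- QoR-15, MFI-20 and the cognitive scores are analysed as numeric paired outcomes. The chi-square rule for psychometric data is removed, and McNemar's test is kept for outcomes that are truly binary and paired.

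The cost is a few sentences of text. No change to data collection, visits or sample size is needed. The rewording should be settled before allocation is revealed to the analysts, so that the choice of test cannot follow the results.

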#### Correction for multiple comparisons

Since it should be assumed that grey-matter changes and changes in DTI are inter-dependable variables, the significance level for each sample size estimation should be corrected for multiple comparisons. The desired corrected significance level is 0.025 (significance level of 0.05 Bonferroni corrected for two number of hypothesis). With a SD of ± 10% and 80% power, this gives a sample size of 30 volunteers regarding detection of statistically significant differences in grey-matter volume. Regarding statistically significant differences in DTI, the calculation gives a sample size of 20 volunteers. We are therefore confident that a sample size of 30 volunteers will be sufficient to ensure the necessary statistical power.

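### The analysis section does not secure 5% error control over the two primary endpoints, and Duncan's procedure does not provide it for the non-MRI secondary outcomes

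*Protocol article*

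**What the plan says.** All references are to the protocol article.

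- **Statistical analysis, on the level:** "The risk for Type I errors is reduced by reducing the significance level to 0.05 (alpha"). No level per primary endpoint is given.
- **Sample size:** "We base our sample size estimations on the following primary end points: (1) changes in grey-matter volume, and (2) DTI changes". The grey-matter calculation starts from 0.05: "applying a two-tailed alpha value of 0.05, SD ± 10% and a desired power of 0.80".
- **Correction for multiple comparisons** (under Sample size): "The desired corrected significance level is 0.025 (significance level of 0.05 Bonferroni corrected for two number of hypothesis").
- **Detection of differences between general anaesthesia methods:** "With a significance level of 0.025 (Bonferroni corrected), SD ± 10% and a power of 80%, the sample size is 20".
- **Statistical analysis, on MRI data:** "correction for multiple comparisons is performed with Bonferroni’s correction or the false discovery rate (FDR"). Both primary endpoints are MRI measures, so this sentence reaches them.
- **Statistical analysis, on secondary outcomes,** where multiple comparisons are unavoidable: "Duncan’s corrections (i.e. secondary outcome parameters) are performed".
- **Secondary outcomes** lists resting-state fMRI, MFI-20, the cognitive tests (PASAT, TAP, CPT3), the quality-of-recovery questionnaire, and correlations between MRI findings and clinical outcomes. **Outcomes** sets four measurement times per session: before and after anaesthesia, day 1 and day 8.

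**The concern.** The sentence on the level is wrong on the protocol's own terms. The sample size sections begin at 0.05 and reduce it to 0.025, so 0.05 is the starting point and not a reduction. A reader who follows the analysis section alone finds 0.05 and nothing that assigns 0.025 to either primary endpoint. A primary p-value between 0.025 and 0.05 then has no clear status: it misses the level used for sizing but meets the only level named for analysis.

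For the non-MRI secondary outcomes the problem is the tool. Duncan's procedure is a range test for pairwise differences among means within one analysis of variance. It lets the joint error grow with the number of means and does nothing about testing several different outcomes. It also does not fit the correlations listed as a secondary outcome, or the Wilcoxon and Mann-Whitney tests that the same section allows. Results would be reported as corrected when they are not.

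**Working it through.** **1. Which level drives the sample size?** Inputs from Sample size and its correction subsection: grey-matter difference 8%, DTI change 10% ("We assume a 10% change in mean diffusivity"), SD 10%, power 0.80. The two-sided normal-approximation formula for two means is

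n = 2 × (z(1−α/2) + z(0.80))² / (difference/SD)², with z(0.80) = 0.8416.

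At α = 0.05, (1.960 + 0.8416)² = 7.849. At α = 0.025, (2.2414 + 0.8416)² = 9.505.

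| Endpoint | α | Calculation | n | Article |
|---|---|---|---|---|
| Grey matter, 8% | 0.05 | 2 × 7.849 / 0.64 = 24.5 | 25 | 25 |
| DTI, 10% | 0.05 | 2 × 7.849 / 1 = 15.7 | 16 | 16 |
| Grey matter, 8% | 0.025 | 2 × 9.505 / 0.64 = 29.7 | 30 | 30 |
| DTI, 10% | 0.025 | 2 × 9.505 / 1 = 19.01 | 20 | 20 |

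All four figures reproduce, so the design level is 0.025 two-sided per endpoint. (This is the formula for independent groups. Whether it suits a trial in which volunteers are their own controls is a separate matter.)

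**2. What if each primary endpoint were tested at 0.05?**

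- Upper bound: 0.05 + 0.05 = 0.10.
- Independent endpoints: 1 − 0.95² = 0.0975.
- Correlated test statistics (simulated): about 0.090 at correlation 0.5 and 0.078 at 0.8.
- For comparison, 0.025 each: at most 0.05; 1 − 0.975² = 0.0494 if independent.

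**3. Does the Bonferroni-or-FDR sentence settle it?** That depends on a family the article does not name.

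- Bonferroni across the two endpoints holds 5%.
- FDR (Benjamini-Hochberg) across only the two endpoints also holds about 5%: simulated 4.4% to 5.0% with no true effects at correlations from 0 to 0.8, and 5.0% with one true effect.
- FDR across many regions or voxels does not hold family-wise error. With half the hypotheses false and strongly detected, the simulated family-wise error is 14% for 10 tests, 24% for 20 and 55% for 60. These test counts are illustrative; the article gives none.

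**4. Duncan's procedure.** The joint level for k means at nominal 0.05 is 1 − 0.95^(k−1).

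- k = 2: 5.0%.
- k = 3: 1 − 0.95² = 9.75%.
- k = 4: 1 − 0.95³ = 14.3%.

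The figure for k = 4 assumes that the four time points of one session are compared as one set, for one outcome. Across outcomes the procedure makes no adjustment. As an illustration, one test at 0.05 on each of the five non-MRI instruments, taken as independent, gives 1 − 0.95⁵ = 22.6%.

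**5. Does holding 0.025 cost sample size?** With n = 30, difference 8%, SD 10% and the same formula: 0.8 × √(30/2) − 2.2414 = 3.098 − 2.241 = 0.857, and Φ(0.857) = 0.804. Power is 80.4%, so N = 30 stands.

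**The case against.** The strongest defence is that 0.05 is the overall level and 0.025 is each endpoint's share. The correction subsection defines 0.025 as 0.05 divided for two hypotheses, and the section on differences between methods uses 0.025 again. The analysis section never says that each primary endpoint is tested at 0.05, and its MRI sentence covers both primaries. On that reading the primary family is held at 5%. This stands as a possible reading. A reader might infer that the plan actually runs the primaries at a 9.75% error rate, or that error control fails for the primary and secondary families alike. The documents do not support either statement: 9.75% is what would follow if no correction were made across the two endpoints, and no section says that. What the defence does not remove is that the sentence calls 0.05 the reduced level, that the 0.025 is stated only for sample size estimation, and that the MRI sentence leaves both method and family open.

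On the secondary outcomes, the plan first refers to limiting repeated comparisons by some general summary, and invokes Duncan only where multiple comparisons cannot be avoided. So 14.3% is conditional. A reader might go further and treat all eight agent-by-time means as one set, which would give 1 − 0.95⁷ = 30.2%; no section specifies such a comparison. A reader might also count resting-state fMRI among the outcomes left to Duncan, but it falls under the MRI sentence, and Data processing – MRI gives it its own corrected threshold.

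Finally, the article is a condensed account with an exploratory aim. Choosing the MRI correction and defining regions or voxels may properly sit in an analysis plan, and strict family-wise control of secondary outcomes is not something the protocol promises. That is fair, and the open choice alone would not be a finding. It matters here because it cannot be relied on to repair the stated level. Naming Duncan is different: it is a stated choice that does not do what it is cited for.

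**Conclusion.** The point holds in two parts of different strength.

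**Primary endpoints: control not secured.** The wording of the level is wrong against the protocol's own sample size sections, and the analysis section does not state the 0.025 on which N = 30 depends. The exposure is a family-wise error between 5% and 10%: 5% if 0.05 is meant as the overall level and split, up to 10% if it is applied to each endpoint. It falls to about 7.8% if the two test statistics correlate at 0.8.

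**Non-MRI secondary outcomes: the named correction does not give family-wise control.** This does not depend on how the level is read. For three or more means Duncan's joint level exceeds 5%, and across different outcomes or correlations it offers nothing. The size within one outcome is 14.3% on the four-time-point assumption.

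Neither part affects the sample size.

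**What to change.** Three sentences in Statistical analysis, settled before any unblinded analysis:

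1. Replace the sentence on the level with a statement that each of the two primary endpoints is tested two-sided at 0.025, or that the two are tested by Holm at an overall two-sided 0.05.
2. State that any correction over regions or voxels is applied within each primary endpoint, in addition to the split between the two, and name one method for it.
3. Replace Duncan with Holm over a listed set of secondary tests. Holm works on p-values, so it covers questionnaire scores, cognitive tests, correlations and rank tests alike. If FDR is preferred, name it and label the results as FDR-controlled, without a family-wise claim.

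The cost is wording only. N = 30 still gives 80.4% power for the 8% grey-matter difference at 0.025 by the protocol's own formula. The downside is that some secondary p-values become less favourable.
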